The OptiBreech 1 opened in January 2021, with 10 sites gradually joining the study throughout 2021 due to delays with R&D approvals affected by the COVID-19 pandemic (https://optibreech.uk/participating-sites/). This is a preliminary observational and qualitative feasibility study, aiming to determine whether there is a demand for vaginal breech birth, whether it is possible to implement the OptiBreech model of care, and how acceptable the OptiBreech model is to women and staff. As of 9 September 2021, a total of 27 women requesting a vaginal breech birth have been recruited to the study across 4 sites. A brief summary table is presented below, comparing our returned results so far, alongside the largest reported study of ECV outcomes in the UK.^40^

Table 2: Results of OptiBreech 1

*OptiBreech 1* – conducted in the hospitals participating in this randomisation study (to 7/9/21)

| **Outcome** | **OptiBreech 1**  *planned vaginal breech births following or without ECV attempt* | **Melo et al 2019 ECV study**  *gold standard UK ECV pathway* |
| --- | --- | --- |
| Total vaginal births | 48% (13/27) | 43.6% (1141/2614) |
| Spontaneous vaginal birth | 44% (12/27) | 33.1% (866/2614) |
| Instrumental birth  *(forceps or suction cup)* | 4% (1/27) | 10.5% (275/2614) |
| Pre-labour caesarean birth | 19% (5/27) | 36.6% (957/2614) |
| In-labour caesarean birth | 33% (9/27) | 18.5% (484/2614) |
| Baby turned head-down prior to labour following failed ECV | 4% (1/27) | 4% (57/1334) |
| Admission to NICU / SCBU* | 4% (1/27) | 3.6% (95/2614) |
| Stillbirth or neonatal death (within 28 days of birth) * | 0 | 0.19% (5/2614) |
| Someone present who had completed physiological breech birth training | 83% (10/12) | *Not reported* |
| Someone present who met all proficiency criteria | 75% (9/12) | *Not reported* |
| Less than 5 minutes elapsed between the birth of the pelvis and the birth of the head | 92% (11/12) | *Not reported* |
| Maternal birth position | Upright – 83% (10/12)  Supine (back) – 17% (2/12) | *Not reported* |

* The OptiBreech 1 study has not collected enough data to make a comparison on these outcomes, but we would expect results to be similar, based on the RCOG Guidance described below.

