## Secondary Outcomes

The following potential primary and secondary outcomes for a substantive trial will be feasibility-tested, and incidence rates will be used to inform power calculations for the substantive trial.

1. Admission to higher-level neonatal care, measured at 28 days following birth, as a binary (yes/no) and continuous (number of days/nights) outcome, from patients’ medical records;
2. Mode of birth measured using patient’s medical records on day of birth, as a categorial measurement to include the following categories: vaginal breech birth, forceps breech, pre-labour CS, emergency CS, cephalic vaginal birth, cephalic forceps, cephalic ventouse;
3. Composite neonatal perinatal death or serious adverse morbidity, measured at 28 days following birth, from patients’ medical notes; serious neonatal morbidity to include the following: 5 minute APGAR score <7, peripheral nerve injury present at discharge from hospital, skull fracture, spinal cord injury, admission to NICU>4 days, intubation/ventilation >24 hours, convulsions >24 hours, parenteral or tube feeding >24 hours;
4. Composite maternal death or serious morbidity, measured at 28 days following birth, from patients’ medical notes; serious maternal morbidity to include the following: postpartum haemorrhage >1000 mL, obstetric anal sphincter injury, cervical laceration involving lower uterine segment, vertical uterine incision or serious extension to transverse uterine incision, bladder, ureter or bowel injury requiring repair, dilation and curettage for bleeding or retained placental tissue, manual removal of placenta, uterine rupture, hysterectomy, vulval or perineal haematoma requiring evacuation, wound dehiscence / breakdown, wound infection requiring prolonged hospital stay / readmission / antibiotics, sepsis, disseminated intravascular coagulation;
5. Use of services following referral for breech care, to include antenatal and postnatal appointments, total time spent admitted to hospital, number of ECVs, number of ultrasound scans, and professionals present at birth, measured at 28 days following birth from patients’ medical notes;
6. Satisfaction with care, measured using previously validated survey questions with a 5-point Likert scale, at 1 month post birth
7. Experience of childbirth, measured using the ‘Childbirth Experience Questionnaire’^59,60^ at 1 month post birth

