| Birth weight | N | * | Standardised procedures | continuous |
| Gap centile | N | * | Standardised tool | continuous |
| Head circumference | N | * | Standardised procedure | continuous |
| Apgar, 1 minute and 5 minutes | N | Outcome | Standardised tool | ordinal |
| Live birth / stillbirth / neonatal death | N | Outcome |  | categorical |
| Date | N | * |  | date |
| Cord blood gases | N | outcome | Standardised tool | continuous |
| Resuscitation required | N | outcome |  | binary |
| Was resuscitation initiated with the umbilicus intact? | N | outcome |  | binary |
| Admission to neonatal unit / special care baby unit / transitional care | N | outcome |  | binary |
| Reason | N | * |  | Categorical |
| Number of nights | N | Economic |  | Continuous |
| Severe morbidity | N | Outcome |  | binary |
| Additional trauma or morbidity | N | Outcome |  | binary |
| Randomised participants only | | | | |
| How much time did someone spend on-call to support this birth? | Staff reported | Economic |  | continuous |
| At any point during labour, did the lead attendant (OptiBreech team member if present) advise a caesarean birth? | N | fidelity |  | binary |
| Was the birth presented to others for teaching purposes, including simulation if appropriate? | Staff reported | fidelity |  | binary |

| Follow-up | | | | |
| --- | --- | --- | --- | --- |
| Survey 1 month following birth | | | | |
|  | Source  P = patient-reported | Why  * = explanatory | Standardised tool or procedure | Form of data |
| I got the information that was relevant to me | P | outcome | 5-point Likert scale based on validated instrument^70^ | continuous |
| I was offered little choice about my care | P | outcome |  | binary |
| I felt I was treated as an individual | P | outcome |  | binary |
| I could discuss what was important to me | P | outcome |  |  |
| I was overwhelmed with the information | P | outcome |  |  |
| The extra care I received made me feel that my baby was safe | P | outcome |  |  |
| The worry nearly became too much for me | P | outcome |  |  |
| When you were pregnant, did you use any of the following to encourage your baby to turn head-down? | P | * |  | categorical |
| Did you have an attempt at turning the baby to head-down by a doctor or midwife, also known as ECV or external cephalic version? | P | * |  | binary |
| If you were pregnant with a breech baby again, would you choose to have an attempt at turning the baby (ECV)? | P | Outcome |  | binary |

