**Randomised to ‘offer ECV’ vs ‘offer OptiBreech care’ (orange)**

1. Potential primary outcome = neonatal admission. In the latest Cochrane Review,^37^ neonatal admission occurs 121/1000 following ECV.
2. Potential secondary outcome = Mode of birth. In the latest Cochrane Review,^37^ CS rate is 180/1000 following ECV.

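### The listed neonatal admission item does not record level of care, so the pilot's admission rate cannot be matched to an undefined outcome or to the protocol's comparison rates

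*Protocol*

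**What the plan says.** **The outcomes.** In the Protocol, section 5 (Secondary Outcomes), item 1 is "Admission to higher-level neonatal care, measured at 28 days following birth, as a binary (yes/no) and continuous (number of days/nights) outcome". Item 3 is a composite of perinatal death or serious neonatal morbidity, taken from the medical notes, and one of its components is "admission to NICU>4 days". The lead-in to the list says that the incidence rates will feed the power calculation of the substantive trial.

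**The data.** Section 12 (Data to be collected, Baby Outcomes) lists "Admission to neonatal unit / special care baby unit / transitional care" as a binary item. After it come a categorical reason and "Number of nights | N | Economic", a continuous item with no split by level of care. A separate binary row, "Severe morbidity | N | Outcome", has no components listed.

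**Other uses of the outcome.** Table 2 in section 4 compares OptiBreech 1 with a published UK ECV cohort on "Admission to NICU / SCBU", with no mention of transitional care. Section 13 (Statistical analysis) gives, for the randomised comparison, "Potential primary outcome = neonatal admission", with a cited rate of 121/1000 after ECV. The Green/Amber/Red section bases its 2280 women on the same outcome. Section 10 (Assessment of safety) puts admission to neonatal care at about 5-7% at term.

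**Safety reporting.** Section 10 (Ethics Reporting) requires NICU stays longer than 4 days to be reported at once as SAEs. It lists NICU stays of up to 4 days among the expected SAEs to be recorded and reported.

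**The concern.** The protocol uses at least two descriptions of one outcome, higher-level care and NICU/SCBU admission, and the listed item matches neither explicitly. It adds transitional care to the NICU/SCBU group and keeps no marker of which setting the baby went to.

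This matters because neonatal admission is the candidate primary outcome of the full trial, and estimating its incidence is a stated purpose of the pilot. Section 12 also gives, as a reason for the data set, the need to pilot collection of every endpoint that a substantive trial may use. An analysis plan can choose a definition, but it cannot recover a level of care that was not recorded. If the definition is settled after data collection and excludes transitional care, the notes would have to be re-abstracted.

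**Working it through.** **1. What each use requires and what the listed items give**

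| Use | Requires | Admission and nights items give |
| --- | --- | --- |
| Secondary outcome 1, yes/no | Admission at whichever levels count as higher-level (not defined) | Admission at any of three pooled levels |
| Secondary outcome 1, nights | Nights at those levels | Nights, not split by level |
| Composite, NICU over 4 days | NICU nights | Not separable from other nights |
| Comparison with Table 2 | NICU or SCBU admission | NICU, SCBU or transitional care |

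Five nights in transitional care and five nights in NICU produce the same two entries. OptiBreech 1 makes the mismatch concrete. Table 2 reports 1/27 of those women under the NICU/SCBU label, while section 6 (OptiBreech mTC) says that OptiBreech 1 records will be entered into the new database, where the pooled item applies.

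**2. The comparison rates and what they mean in 104 women**

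- Table 2: 95/2614 = 3.6%, and 104 × 0.036 = 3.7 admissions.
- Safety section: 5-7%, and 104 × 0.05 = 5.2 to 104 × 0.07 = 7.3.
- Section 13: 121/1000 = 12.1%, and 104 × 0.121 = 12.6.

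The highest rate is more than three times the lowest (12.1/3.6 = 3.4). The protocol does not say how far the gap reflects definition and how far population. A pilot rate without level of care cannot show which of these figures it should be set against.

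**3. Sensitivity of the rate to the definition**

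Let f be the share of recorded admissions that are transitional care only. The documents do not give f, so it is an assumption shown as a range. Rate without transitional care = recorded rate × (1 − f). For a recorded 12.1%:

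- f = 10%: 0.121 × 0.90 = 10.9%
- f = 25%: 0.121 × 0.75 = 9.1%
- f = 50%: 0.121 × 0.50 = 6.1%

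**4. What that would mean for planning (illustration only)**

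The protocol's 2280 cannot be reproduced, because it states no significance level, power, or difference or margin. As an illustration, assume a one-third relative reduction, two-sided 5% and 80% power:

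n per arm = [1.96√(2p̄(1−p̄)) + 0.842√(p₁(1−p₁) + p₂(1−p₂))]² / (p₁−p₂)²

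With p₁ = 0.121, p₂ = 0.0807 and p̄ = 0.1008, this is (0.8346 + 0.3576)² / 0.0403² ≈ 874 per arm, or 1748 in total. With p₁ = 10.9%, 9.1% and 6.1%, the totals are 1964, 2398 and 3694. The definition therefore matters for planning, but without f no single figure can be attached to it.

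**5. Other routes to NICU over 4 days**

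The SAE rules capture NICU stays on both sides of the 4-day cut. The severe-morbidity item may also capture the long stays, although its components are not listed. Neither route gives special-care against transitional-care counts, or nights at each level, for secondary outcome 1. No section names the SAE reports as the source of the composite.

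**The case against.** The strongest reply is that section 12 is the only place that spells out which settings count, so it can be read as the working definition, with transitional care included on purpose. On that reading nothing is over-counted. This stands: a reader might infer that the item plainly inflates the outcome, but that presumes a definition the protocol does not contain. The Table 2 label describes earlier data beside a published cohort and does not define this study's outcome. The inconsistency between the descriptions remains.

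A reader might also infer that NICU over 4 days is lost altogether, or that transitional-care stays will enter the serious-morbidity composite. The documents support neither. SAE reporting covers long NICU stays, severe morbidity is a separate item, and nothing says that the composite is computed from the pooled nights. What stands is narrower: the two listed items cannot supply the component alone, and its source is not tied down beyond the medical notes.

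A third inference, that the full trial would be undersized by some stated amount, does not hold either. It would follow only if the full trial used a narrower outcome than the pilot counted, and its size depends on an unknown share.

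Two further replies carry some weight. Section 12 is a data listing and the eCRF is not shown, so sub-fields may exist. The pilot is also imprecise: 4 admissions in 104 (3.8%) has an exact 95% interval of 1.1% to 9.6%, which hides modest differences in definition. Sampling error shrinks in a larger data set, however, while a difference in definition does not.

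**Conclusion.** The point holds in a limited form and should be acted on. As listed, the data cannot identify admissions that were transitional care only, the outcome they serve is undefined, and the resulting rate cannot be matched to 3.6%, 5-7% or 12.1%. The rate overstates higher-level care only if transitional care is not meant to count. The size of any overstatement is unknown. The reductions from 12.1% to between 10.9% and 6.1% rest on assumed shares of 10% to 50%.

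The conclusion assumes that the section 12 listing is what will be collected. If the eCRF already records level of care and nights by level, what remains is to define the term and name the source of the NICU component.

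**What to change.** - Replace the pooled item with the highest level of neonatal care reached (NICU, special care, transitional care, none, and any further level that sites use), and record nights at each level.
- State in secondary outcome 1 which levels count as higher-level neonatal care, and use the same definition in section 13 and in the Green/Amber/Red section.
- Report the admission rate with and without transitional care, so that it can be set beside each comparison rate.
- Derive NICU over 4 days from NICU nights, cross-check it against the SAE reports, and list the components of the severe-morbidity item.

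The cost is a small eCRF change and slightly more abstraction from notes that are reviewed anyway. The planned CRF pilot on OptiBreech 1 records is a natural place to make it, since section 6 already allows for refinements at that stage. Made after recruitment, the change would mean returning to the notes.

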## Data quality and validity

We will conduct at least one site visit with each participating site. The purpose of this visit will be to provide training, review the site file and check the data in a sample CRF against anonymised clinical notes. Where discrepancies are noted, we will provide support to the site and return if necessary. A record of these visits and findings will be kept. We will also use them to develop and pilot an audit form to identify potential issues that should be checked during any future substantive trial.

## Data handling and record keeping

The local PI is responsible for data collection, recording and quality, unless otherwise delegated to a member of the local research team and recorded on the delegation log. All investigators and study site staff involved with this study must comply with the requirements of the Data Protection Act 2018 with regard to the collection, storage, processing and disclosure of personal information and will uphold the Act’s core principles.

Data will be collected via an eCRF directly onto a database maintained by MedSciNet, using a secure login and password. Paper-based CRF forms will be provided to facilitate data collection prior to entry, where this is preferrable for sites or for participants. Anonymised data will be downloaded from the database at the end of the study period.

All data, and scanned copies of paper-based CRFs where these have been used, these should be submitted to the research team within 6 weeks of the birth, using either an encrypted NHS e-mail transfer ([contact]) or the Trust’s secure file transfer system. Here it will be kept on a secure computer file on the KCL secure online storage network. Computers used to collate and analyse the data will have limited access measures via user names and passwords. Study sites will keep their hard files for the usual duration after the end of study at their site.

Published results will not contain any personal data that could allow identification of individual participants.

As this is a study involving pregnant women and research records should be retained according to NHS Guidelines for the retention of documentation involving pregnant women. All medical records will be retained for at least 25 years after publication of the final study report. We plan to retain all research data for 10 years, because this is the potential follow-up timeframe stipulated on the consent form.

Following the end of the study, anonymised data will be archived on the university’s secure Sharepoint site. This will be accessible only to the research team.

Anonymised data will be stored in a Microsoft Excel Spreadsheet. All person-identifiable information will be removed or altered. For example, all dates will be converted to time-to-event intervals from the estimated date of birth, or actual data of birth for follow-up surveys. Prospective consent is obtained to use anonymised data in future studies, subject to appropriate ethics and data access approvals.

## Anonymisation of data

Confidentiality will be maintained by use of a Patient Details Database, which is a separate, but linked database. Each participant will be allocated a study code, which will link the two datasets, in case patient details are required for future contact as consented or for data queries. When participant identifiers (first name, last name, date of birth, hospital number, NHS number, etc.) are entered into the MedSciNet database at enrolment (for woman/birthing person), or following the birth (for baby), this information will be automatically and immediately transferred from the main database to the Patient Details Database. In this database, personal details will be stored separately and encrypted, for GCPR-compliant security.

Access to the Patient Details Database will be by separate login. While each local Data Collection Centre will have access to its own participants’ personal data, only the Project Lead and Project Manager will have access to the main file. No personal details will be transferred to a third party for any reason.

# Statistical considerations

The sample size calculation for this pilot trial was carried out by the CI, [name], under the supervision of [name], Senior Clinical Research Epidemiologist at King’s Health Partners Institute of Women and Children’s Health.

## Sample size calculation

The sample size of 104 women was calculated to enable estimation of a recruitment rate between 20-80%, with a 95% confidence interval, within $\pm$10%.

We expect the pilot trial to last 6 months, in 5 NHS sites, with a minimum of 10 recruits per site. In the five months after the first OptiBreech 1 site opened, over 22 women were recruited who wished to plan a vaginal breech birth. This is from a much smaller recruitment pool (only women who know they would like to plan a vaginal breech birth) than the OptiBreech Care Trial, in which all eligible women are invited to participate.

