## Primary Outcomes

1. Recruitment rate recorded as the number of eligible participants who consent to participate in the study by 6 months (randomised) and overall (non-randomised);
2. Acceptance rate recorded as the number of participants randomised to OptiBreech Care who plan a vaginal breech birth, and the number of participants randomised to the control who attempt an ECV, measured at the time of birth;
3. Attrition rate recorded as the number of participants who consent to participate who remain in the study until the end of follow-up at 4 months after birth;
4. Long-term attrition rate recorded as the number of OptiBreech 1 participants who complete 1-year and 2-year follow-up surveys when invited;
5. Fidelity to intervention recorded as number of planned VBBs attended by a proficient team member, measured at the time of birth;
6. Costs to deliver the service recorded as total number of days and nights spent on call to support planned VBBs in the trial by 6 months.

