# Study procedures

## Participant recruitment

OptiBreech cohort sites should establish their own pathways for screening, approaching and consenting potentially eligible women and birthing people. An ideal pathway would look like this (Figure 1):

1. Breech presentation is suspected on palpation. The woman is referred for an ultrasound scan to confirm. When a clinician makes a referral, the woman should be directed to the information, including the approved Participant Information Sheet, available on the feasibility study’s website (https://optibreech.uk).
2. Women booked for a presentation scan are initially screened by a member of the clinical team providing direct clinical care, and those eligible for recruitment are flagged.
3. Breech presentation is confirmed on ultrasound. Immediately after this scan, the woman is asked if she would like to participate in the study. She is offered an opportunity to ask questions and consent is obtained, by the staff member if authorised to collect consent on the delegation log, or a member of the research team.
4. If the woman is also eligible to be randomised to standard care or OptiBreech care, based on the consents she has given and her scan results, she is randomised. The woman should receive a copy of all relevant Participant Information Sheets and a copy of her fully executed consent form.
5. She begins the care pathway she is randomised to. A copy of the GP letter, relevant Participant Information Sheet(s) and Consent form is sent to the GP.

This is ideal because OptiBreech care is a care pathway intervention, and the care pathway begins when the woman is first counselled.

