Eligibility for randomisation among the cohort participants is automatically captured in the eCRF during the recruitment process. We are opting not to use an additional screening log, although individual sites may wish to create their own, as this information is already automatically captured on Edge. Having an additional log has not been shown to increase recruitment but does add significantly to the research team’s workload.^63^ Instead, we will monitor site activity through absolute recruitment and adherence rates. We will use a delegation log, and all local research team members involved in recruitment should be listed on this log once the local PI has ensured they have received training. As this is an intervention study, all those taking consent for participation in the study should have current GCP training in place, or have completed the OptiBreech training that includes GCP-lite training relevant to this study, and be listed on the delegation log.

Consent will be completed directly through the study’s on-line database, provided by MedSciNet. The consent form is available in an electronic format on the study database to which participants have direct access, and they will sign consent online. Access will be provided via the e-mail address given by potential participants for this purpose. The system will confirm who accessed the database and the date. The consent form will be countersigned by separate access by the person taking consent, so that the data and time are recorded. This may be completed face-to-face or asynchronously through the online access provided. A fully executed version is saved within the database. A copy is exported to be stored in the participant's medical record, and the participant can download a copy for their own records using their direct access.

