## Randomisation Procedures

A total of 104 participants eligible for randomisation, who have consented to randomisation, will be automatically randomised to either OptiBreech Care or the control (standard care). The randomisation schedule will be computer-generated, using MedSciNet software. Allocation will be automatic during the enrolment process on the database and revealed to the person who is taking consent and enrolling the participant onto the study. All local research team members who are authorised to take consent will have login information to complete this process. Therefore, randomisation can only occur when one of them is available, at the earliest opportunity after the breech presentation is diagnosed.

Minimalisation factors will include site, parity (0 vs 1 or more previous births), type of breech presentation (extended/frank vs any other), and gestation at enrolment (<36 weeks, 36-38+6, 39+ weeks). Allocation between arms will be equal. The enrolment log will be completed automatically through the database.

Due to the two-stage consent process developed in collaboration with the PPI group, women randomised to the control will be cared for within the standard local care pathway, without any further steps in the consent process.

Women randomised to OptiBreech Care will be informed they have been randomised to OptiBreech Care, given the OptiBreech Care Information Sheet (paper or on-line version), and scheduled for counselling by a member of the OptiBreech team as per the Description of Intervention below. Consent for mode of birth is a standard part of all antenatal care, and national guidelines recommend that women should be offered the option of a vaginal breech birth, so further specific consent to receive specialist OptiBreech care will not be taken. Instead, women will be informed that they can request to see another member of the team at any point.

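### The 104 is justified as the denominator of a recruitment rate but used as the number randomised, and the rate has no defined denominator that counts women who decline the cohort

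*Protocol*

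**What the plan says.** The Protocol's Sample size calculation gives one justification for the trial's size: "The sample size of 104 women was calculated to enable estimation of a recruitment rate between 20-80%, with a 95% confidence interval, within" ±10%.

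Elsewhere the same number is the count of women who have already agreed. Randomisation Procedures says "A total of 104 participants eligible for randomisation, who have consented to randomisation, will be automatically randomised". The Summary lists 104 women randomised plus an estimated 50 not randomised. End of Study Definition closes recruitment once 104 women are in the pilot trial. No section sets a target for the number eligible or invited.

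Primary Outcomes, item 1, reads "Recruitment rate recorded as the number of eligible participants who consent to participate in the study by 6 months" for the randomised part. Statistical analysis repeats this and names the OptiBreech mTC Database as the source of the reported figures.

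On the denominator, Participant recruitment says that eligibility for randomisation is captured in the eCRF for women in the cohort. It then says "We are opting not to use an additional screening log", leaves sites free to keep their own, and gives as the reason that the information is already on Edge. It adds: "Instead, we will monitor site activity through absolute recruitment and adherence rates". Under Cohort Exclusion criteria, women who do not consent to contribute data are outside the cohort.

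**The concern.** A recruitment rate is a proportion: women who agree, divided by eligible women who were asked. A precision statement for a proportion refers to its denominator. Here the precision statement is attached to the number who agreed.

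Two things follow. First, the sample-size paragraph does not describe the design that will be run. Second, the first primary outcome is called a rate but is recorded as a number, and part of its natural denominator is missing from the named source. An eligible woman who refuses the cohort altogether leaves no record in that database.

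The Protocol lists recruitment rates among the quantities meant to inform a full RCT (Objectives, trial delivery and design). Under Sites it assumes that about half of eligible women will consent to randomisation. That assumption is what a pilot should test. If the women who decline are never counted, no later analysis plan can recover them.

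**Working it through.** **Inputs.** n = 104, rate anywhere from 20% to 80%, 95% confidence, half-width 10 points (Sample size calculation). Equal allocation, so 52 per arm (Randomisation Procedures). About half of eligible women expected to consent (Sites). Worked example of 22 of 52 and 32 of 52 accepting their allocation, from 52 − 30 and 52 − 20 (Green/Amber/Red Criteria).

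**1. Reproducing 104.** For one proportion at the worst case, p = 0.5:
- Exact (Clopper-Pearson): half-width 10.02 points at n = 103 and 9.97 at n = 104. So 104 is the smallest n within 10 points.
- Wald: 1.96² × 0.25 / 0.10² = 96.04, so 97. At n = 104 the half-width is 1.96 × √(0.25/104) = 9.6 points.
- Wilson needs about 93, and Wald with continuity correction needs 106.

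The exact method returns 104, so the arithmetic is sound. In every variant, n is the denominator.

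**2. If 104 really were the denominator.** The number randomised would be 104 × r: about 21, 52 or 83 women at r = 20%, 50% or 80%. That is not the planned trial.

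**3. With 104 as the numerator, as the design has it.** The eligible pool is N = 104/r, and the half-width is 1.96 × √(r(1 − r)/N).

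| True rate r | Eligible women N | Half-width |
| --- | --- | --- |
| 20% | 104/0.2 = 520 | 3.4 points |
| 50% | 104/0.5 = 208 | 6.8 points |
| 80% | 104/0.8 = 130 | 6.9 points |

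Substituting N gives 1.96 × √(r²(1 − r)/104), which is largest at r = 2/3, at 7.4 points. On the Protocol's own expectation of about one half, 104 randomised women require about 208 eligible women.

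**4. What the database can and cannot supply.** Let f be the share of eligible invited women who join the cohort, and g the share of eligible cohort members who accept randomisation. The database yields g. Uptake among all eligible women invited is f × g. The database figure is therefore too high by a factor 1/f whenever f is below 1. The Protocol gives no value for f, so the size of the overstatement cannot be stated.

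**5. Proportions for which 104 or 52 is the denominator.**
- All randomised women (retention, pooled acceptance), n = 104: ±9.6 points Wald or ±9.97 exact, at 50%.
- Acceptance within one arm, n = 52: 1.96 × √(0.25/52) = ±13.6 points at 50%, and ±10.9 at 20% or 80%. The Protocol's worked example gives 22/52 = 42% ± 13.4 and 32/52 = 62% ± 13.2.

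**The case against.** The strongest reply is that little depends on this rate. The Green/Amber/Red formula uses acceptors per site-month, pooled over arms and net of losses to follow-up. No proportion of eligible women enters it. The primary objective in the Summary asks how many women will consent, and site monitoring is by absolute numbers. This stands, and it limits the weight of the point.

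The Protocol also does not ignore the denominator. Women who join the cohort but decline randomisation are recorded, and The OptiBreech-ECV Trial section plans a comparison with them. Edge is named as already holding the information. A reader might infer that the denominator is not collected at all, and the documents do not support that. What remains is narrower. The remark about Edge follows a sentence about cohort participants, nothing says that Edge holds women who refuse the cohort, and Statistical analysis does not use it as a source.

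Three other stronger readings also fail:
- A reader might infer that the trial is too small for its recruitment rate. With a known denominator it is more precise than claimed.
- A reader might take the arm-level ±13.6 points as contradicting the stated ±10. The ±10 is promised only for the recruitment rate, and no precision is stated by arm.
- A reader might divide 104 by the planned total of 154 and treat the result as the recruitment rate. The 50 is an estimate with no minimum, and the non-randomised group includes OptiBreech 1 women and women ineligible for randomisation.

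**Conclusion.** The point holds in limited form. The number 104 is correctly calculated for a proportion with 104 women in its denominator, but the design uses it as the number who consented and were randomised. Read that way, the half-width runs from 3.4 points at 20% to at most 7.4 points, so the fault is a mismatched justification and not a shortage of women. These half-widths assume that the number of eligible women invited is known.

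Separately, the first primary outcome has no stated denominator, and eligible women who decline the cohort are absent from the database named as its source. A rate computed from that database alone describes cohort joiners and overstates uptake among all eligible women invited, by an amount that the Protocol does not allow one to calculate. This assumes that Edge does not hold those women or will not be used. If it does and is used, the gap closes.

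This should be corrected before recruitment opens, because uncounted refusals cannot be recovered afterwards. It does not affect the progression decision.

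**What to change.** 1. In Primary Outcomes and Statistical analysis, define the recruitment rate as women randomised divided by women with ultrasound-confirmed breech who meet all randomisation criteria other than consent and are invited. Include self-referrals and breech found on scans done for other reasons. The words other than consent matter, because consent is itself listed as an inclusion criterion.
2. Obtain that denominator as one aggregate count per site per month, or from Edge once it is confirmed that Edge holds women who decline the cohort. The step in Participant recruitment at which "those eligible for recruitment are flagged" is not enough alone: it belongs to a pathway described as ideal, comes before breech is confirmed, and misses the other routes of entry.
3. Report uptake of randomisation among eligible cohort members as a separate figure.
4. Reword Sample size calculation to say that 104 randomised women give about ±10 points (9.97 exact, 9.6 Wald, at 50%) for proportions of all randomised women, such as retention or pooled acceptance. Add for information that acceptance within an arm of 52 is estimated to about ±13.6 points at 50%.

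The cost is one count per site per month and a few reworded sentences. No per-woman screening log is needed, and the target of 104 does not change.
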